### Intervention timeline and study organization

The intervention period will span three months, following the baseline assessments of clinical, clinimetric, and biomarker variables (Figs 1 and 3).

Due to anticipated challenges in participant recruitment, the study is planned to be conducted in two separate phases, each involving approximately half of the total sample. These phases are scheduled for September to December 2025 (Chile) and January to April 2026 (Spain), respectively.

### Sample size

The sample size has been previously calculated through the G-Power program, assuming an effect size of 0.35 for the primary outcome, a statistical power of 80% and an alpha error probability of 0.05. This showed that at least 22 participants per group are needed. Assuming a dropout rate of 10–15%, a total of 50 participants is intended. This analysis is based on a previous study on this topic [62].

### Allocation and randomization

Individuals meeting the inclusion criteria will be randomly allocated to one of two treatment arms: (1) IVR plus exercise or (2) exercise alone.

Each patient will be assigned an alphanumeric code for identification, thus respecting their anonymity. To carry out the simple randomization procedure, the principal investigator will receive a list of the alphanumeric codes of the participants and will carry out a random assignment of the subjects in the 2 intervention groups using the SPSS statistical program. Allocation concealment will be ensured using opaque, sealed envelopes. A designated research assistant, independent of the assessment team, will open each envelope to assign participants to their respective intervention or control groups.

Participants will be randomized into intervention and control groups using a predefined randomization scheme, following the provision of informed consent and confirmation of clinical eligibility.

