#### Biomarkers.

Venous blood samples will be drawn from the antecubital vein, centrifuged, aliquoted, and stored at –80°C until analysis. These procedures will be carried out at the Exercise Physiology Research Laboratory of the UFV by external laboratory nurses from Eurofins Megalab, who will be responsible for both sample collection and biomarker analysis. The biomarkers to be analyzed include:

C-reactive protein (CRP), an oxidative stress and inflammation marker.Calcitonin Gene-Related Peptide (CGRP), a neuropeptide involved in the modulation of nociceptive signalling and that has been shown to represent a neurobiological marker of chronic pain and inflammation [37].

Biomarkers measurements will only be made on the Spanish arm of the study, and not in the Chilean arm. This decision was driven by logistical and budgetary constraints. In this respect, biomarker-related analyses will be explicitly stratified, and results will be presented separately for the Spanish sample.

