### Statistics

Data analysis will be performed using SPSS version 30.0 (SPSS Inc., Chicago, IL, USA). Descriptive statistics will be used to summarize the demographic characteristics and baseline clinical, clinimetric and biomarker measurements of the sample. Continuous variables will be reported as mean ± standard deviation (SD), while categorical variables will be presented as frequencies (n) and percentages (%). For quantitative variables that do not follow a normal distribution, the median and interquartile range (IQR) will be used to describe the data.

For the primary analysis, a linear mixed-effects model will be used to compare changes in the dependent variables across the three time points between the two groups. The model will include fixed effects for site (Spain vs Chile) and baseline pain scores, along with group, time, and their interaction, as well as random intercepts for participants to account for within-subject correlations.

In addition to the primary analysis, bivariate correlation analyses (Pearson or Spearman, depending on the distribution of the variables) will be performed to examine the associations between the key variables at each time point.

To explore potential confounding variables, a series of covariate analyses will be performed, adjusting for baseline values of the dependent variables, age, gender, and other relevant demographic or clinical characteristics.

Statistical significance will be set at a p-value of <0.05 for all tests. Effect sizes (Cohen’s d) will be calculated for the main effects of the intervention to assess the magnitude of the group differences, and results will be presented with 95% confidence intervals.

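### Simple randomisation of about 50 people, with no blocking or stratification by site, leaves the Spain-only biomarker sample open to an avoidable uneven split

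*Protocol article*

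**What the plan says.** The Allocation and randomization section names the method and the person who runs it: "To carry out the simple randomization procedure, the principal investigator will receive a list of the alphanumeric codes of the participants", and the same person "will carry out a random assignment of the subjects in the 2 intervention groups using the SPSS statistical program". The only further description is this: "Participants will be randomized into intervention and control groups using a predefined randomization scheme". No section mentions blocks or stratification.

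The same section gives two safeguards: "Allocation concealment will be ensured using opaque, sealed envelopes", and "A designated research assistant, independent of the assessment team, will open each envelope to assign participants". The Blinding section adds that those who deliver treatment do not assess outcomes, and that the biostatistician does not know the allocation.

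Other sections bear on the choice:
- Study setting gives a 1:1 ratio.
- Sample size says that "at least 22 participants per group are needed" and sets a total of 50 to cover 10–15% dropout.
- Intervention timeline and study organization runs Chile from September to December 2025 and Spain from January to April 2026, with roughly half the sample in each.
- Biomarkers states: "Biomarkers measurements will only be made on the Spanish arm of the study".
- Statistics states: "The model will include fixed effects for site (Spain vs Chile"), and adds baseline pain, group, time and their interaction.

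**The concern.** Simple randomisation is valid and unbiased, but it does not control the arm sizes in a small sample. Here the sample is divided by site, and site coincides with calendar period. One set of outcomes, CRP and CGRP, is analysed in Spain alone, in about 25 people. The plan treats site as important enough to model but does not use it in the allocation.

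The site term cannot help the biomarker analysis, because site is constant within Spain. If chance gives that analysis an arm of 8 or 9, some precision is lost and single participants weigh more heavily.

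A smaller matter is who makes the list. The principal investigator trained the assessors at both sites (Results section) and shares oversight with study staff in place of an independent committee (Data monitoring section). The plan separates treatment, assessment and analysis, but does not separate sequence generation from the trial lead in the same way.

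**Working it through.** **Inputs.** From the article: total 50, ratio 1:1, 22 needed per group, dropout 10–15%, about half the sample per phase, biomarkers in Spain only. Assumed: 25 in Spain (range 24–26), and *simple* read as an independent fair draw for each person, so that arm size follows Binomial(n, 0.5).

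**The plan's own total.** 2 × 22 = 44. Dividing by 0.90 gives 48.9, so 49; dividing by 0.85 gives 51.8, so 52. The planned 50 lies between them and matches 12% dropout, since 44/50 = 0.88. The 22 itself can be reproduced only with a test and a correlation that the article does not state (for example a between-group repeated-measures test with f = 0.35, four assessments and correlation 0.5, which gives power 0.818). Nothing below depends on it.

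**Spain: chance of an uneven split.** This is 2 × P(X ≤ k) for X ~ Binomial(n, 0.5).

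| n in Spain | Split or worse | Probability |
|---|---|---|
| 24 | 9:15 | 30.7% |
| 25 | 9:16 | 23.0% |
| 25 | 8:17 | 10.8% |
| 25 | 7:18 | 4.3% |
| 26 | 9:17 | 16.9% |

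**Spain: cost of such a split.** Efficiency relative to equal arms is 4ab/(a+b)².
- 12:13: 4 × 156/625 = 0.998
- 9:16: 4 × 144/625 = 0.92
- 8:17: 4 × 136/625 = 0.87

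For a simple two-group t-test (two-sided 5%, 80% power), the detectable standardised difference is about 1.18 at 12:13, 1.22 at 9:16 and 1.26 at 8:17. The planned mixed model would give other absolute values, but the ordering shows the scale. The average efficiency over all splits is 1 − 1/n = 1 − 1/25 = 0.96.

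**Primary outcome: average cost.** Measure the information by the effective size per arm, 2ab/(a+b).
- Simple randomisation: if N people are retained, the expected effective size is (N − 1)/2. At 12% dropout the mean N is 44, giving 43/2 = 21.5.
- Exact 25:25 start with random dropout: the expectation is (25/49)(N − 1), giving 25 × 43/49 = 21.9.

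The difference is 0.4 of a participant per arm.

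**Is 22 in each arm a threshold?** The smaller arm of 50 starts below 22 with probability 2 × P(X ≤ 21) = 32.2%. But 21:29 has effective size 2 × 21 × 29/50 = 24.4 per arm, and 18:32 has 23.0. At 17:33 it is 22.4 and at 16:34 it is 21.8. So before dropout the effective size falls below 22 only at 16:34 or worse, which has probability 1.5%.

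**The case against.** The strongest reply is that simple randomisation is legitimate and the plan already covers most of the risk. Much of this stands. The site term adjusts the primary analysis for site and, because phase coincides with site, for calendar period too. The biomarkers are secondary, and the Discussion calls those findings preliminary. The Spanish analysis is weak mainly because it has about 25 people, which blocking does not change.

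The binomial figures also rest on a reading. An SPSS draw from a list can fix the number per arm, and if that were done separately for each site's list, the imbalance would largely disappear. The article does not say so, and the word *simple* points the other way.

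A reader might infer three stronger things, none of which the article supports:
- **That the 32% chance of an arm below 22 is a loss of power.** It is not, because precision depends on both arm sizes together, as shown above. The same applies to the chance that both arms keep 22 after 12% dropout (17% with simple randomisation, 42% from 25:25). Even perfect balance fails that test more often than not.
- **That allocation concealment is absent or broken.** Opaque sealed envelopes, an assistant independent of the assessors and a blinded statistician are all planned. No section says that the principal investigator enrols, treats or assesses; training assessors is not assessing.
- **That site imbalance biases the primary estimate.** Allocation is random and site is in the model.

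**Conclusion.** The point holds as a worthwhile but modest improvement. The method is stated, does not use the trial's own site structure, and can be replaced cheaply. The gain lies mainly in the Spanish biomarker sample: a 23% chance of 9:16 or worse with 25 participants (17% to 31% for the nearest comparable splits with 26 and 24), at 8% to 13% loss of efficiency for splits of 9:16 to 8:17. For the primary outcome the average gain is about 0.4 effective participants per arm. These sizes assume independent 1:1 draws, 24–26 people in Spain and, for the primary outcome, 12% dropout. Who generates the list is a secondary matter of separating roles.

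**What to change.** In Allocation and randomization, replace simple randomisation with computer-generated permuted blocks of randomly varying size, stratified by site. Prepare one list per site before that site enrols. Keep the opaque sealed envelopes and the independent assistant. The site term already in the primary model then matches the allocation.

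With blocks of 2 and 4, arms differ by at most 2 within a site and at most 4 overall; with 25 per site, each site ends 12:13. If Chile is already randomised, report that allocation as it was done and use the new scheme for Spain, where most of the benefit lies. If the existing procedure already fixes the numbers per arm within each site, say so instead.

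Have the lists generated by existing staff other than the principal investigator, who do not enrol, treat, assess or oversee participants, for example at the partner university.

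The cost is a new list per site and notification of the change to the ethics committees and the registry. The downside is slight predictability at the ends of blocks, since treatment is not masked; varying the block size and not disclosing it to recruiting staff limits this.

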### Blinding

Due to the nature of the interventions, blinding of participants and treating physiotherapists is not feasible. However, the investigators responsible for delivering the interventions will be different from those conducting the outcome assessments, ensuring a single blind design. An independent biostatistician will also conduct the statistical analysis of the results without prior knowledge of participant group allocation.

### Data retention

To support participant adherence and ensure completion of all trial phases, a structured retention plan will be implemented. Participants will be provided with comprehensive yet accessible information outlining the trial’s objectives, interventions, potential risks, and benefits. Transparent communication will be prioritized through open channels between research staff and participants, encouraging trust and engagement. Regular reminders via phone or email will be used to maintain contact and address any concerns. In-person visits will be scheduled with flexibility to minimize inconvenience and maximize follow-through.

### Data management

All study data will be securely stored in a password-protected, encrypted database with access limited to authorized personnel. To ensure accuracy, data entry will follow a double-entry process and built-in validity checks will be applied. Regular data backups and secure file transfer protocols will be implemented in compliance with institutional and legal data protection standards.

### Statistics

Data analysis will be performed using SPSS version 30.0 (SPSS Inc., Chicago, IL, USA). Descriptive statistics will be used to summarize the demographic characteristics and baseline clinical, clinimetric and biomarker measurements of the sample. Continuous variables will be reported as mean ± standard deviation (SD), while categorical variables will be presented as frequencies (n) and percentages (%). For quantitative variables that do not follow a normal distribution, the median and interquartile range (IQR) will be used to describe the data.

For the primary analysis, a linear mixed-effects model will be used to compare changes in the dependent variables across the three time points between the two groups. The model will include fixed effects for site (Spain vs Chile) and baseline pain scores, along with group, time, and their interaction, as well as random intercepts for participants to account for within-subject correlations.

In addition to the primary analysis, bivariate correlation analyses (Pearson or Spearman, depending on the distribution of the variables) will be performed to examine the associations between the key variables at each time point.

To explore potential confounding variables, a series of covariate analyses will be performed, adjusting for baseline values of the dependent variables, age, gender, and other relevant demographic or clinical characteristics.

Statistical significance will be set at a p-value of <0.05 for all tests. Effect sizes (Cohen’s d) will be calculated for the main effects of the intervention to assess the magnitude of the group differences, and results will be presented with 95% confidence intervals.

### Statistical population and handling of missing data

Primary analyses will follow the intention-to-treat principle, including all randomized participants as allocated, regardless of adherence or dropout. To handle missing outcome data, we will use linear mixed-effects models, which provide valid inference under the assumption that data are missing at random (MAR). However, we recognize that MAR may not always hold. If data exploration or external information suggests a missing not at random (MNAR) mechanism, we will conduct sensitivity analyses using pattern-mixture models or selection models to assess the robustness of our findings.

Biomarkers will be analyzed exclusively within the Spanish cohort, as these measures are not collected in Chile. All biomarker-related analyses will therefore be site-specific and reported separately. For these outcomes, linear mixed-effects models will be applied with time (baseline, 1-month, and 3-month) as a repeated factor and group (IVR + exercise vs exercise alone) as a fixed factor, including random intercepts for participants. Effect sizes and 95% confidence intervals will be presented. Missing biomarker data will be handled within the same mixed-model framework under MAR assumptions, with sensitivity analyses for MNAR scenarios as described above.

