## Results

According to the recommendations of the Initiative on Methods, Measurement, and Pain Assessment in Clinical Trials (IMMPACT), this study will incorporate multiple measures to evaluate changes in pain intensity, health-related quality of life and functioning, as well as global ratings of improvement [41]. Similarly, the assessment of domains will follow expert consensus from the OMERACT Shoulder Working Group, aligned with the Core Domain Set for Shoulder Disorders [42].

Clinical and clinimetric outcomes will be assessed at baseline and at follow-ups at 1-, 2- and 3-months following treatment initiation. Biomarkers will be measured at baseline and at 1- and 3-months follow-ups (Figs 1 and 3).

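### The biomarker model, as stated, lists no group-by-time term and no baseline covariate; fitted that way, its group coefficient estimates only two-thirds of the mean follow-up effect

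*Protocol article*

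**What the plan says.** The protocol article describes two mixed models.

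- **Main model** (Statistics). In a sentence that introduces the primary analysis, the article states that "a linear mixed-effects model will be used to compare changes in the dependent variables across the three time points between the two groups". Its terms are "fixed effects for site (Spain vs Chile) and baseline pain scores, along with group, time, and their interaction", with random intercepts for participants.
- **Biomarker model** (Statistical population and handling of missing data). This covers the Spanish participants only and is described "with time (baseline, 1-month, and 3-month) as a repeated factor and group (IVR + exercise vs exercise alone) as a fixed factor". It also has a random intercept for each participant. No other term is listed.

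The Results section gives the visits: "Biomarkers will be measured at baseline and at 1- and 3-months follow-ups". So one of the three levels of time in the biomarker model precedes treatment.

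On covariates, Statistics adds that "a series of covariate analyses will be performed, adjusting for baseline values of the dependent variables, age, gender", among other characteristics. This step is presented as an exploration of confounding. The Discussion says that adjustment covariates will be prespecified in the statistical analysis plan, and it calls the biomarker findings preliminary.

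**The concern.** A longitudinal model with baseline among its responses usually estimates the treatment effect through the group-by-time interaction: how much more one group changes than the other. The main model names that term. The biomarker model, written out separately, names only the two main effects and has no baseline covariate that could take the interaction's place.

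If an analyst fits what is written, the only group comparison available is the group main effect. That is an average over visits, one of which cannot carry a treatment effect. The promised effect sizes and confidence intervals would then describe a quantity that is smaller than the treatment effect and mixed with baseline chance differences. The biomarker sample is only about half of 50 participants, so little precision can be spared.

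**Working it through.** The plan gives no biomarker effect size, variance, correlation or power, so there is no stated figure to reproduce. The dilution follows from the model; the power figures need assumptions.

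**1. What the group coefficient estimates.** Let D0, D1 and D3 be the group differences in means at baseline, month 1 and month 3. With time and group as main effects, a random intercept and complete data, the group coefficient is

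(D0 + D1 + D3) / 3.

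Randomisation makes the expected D0 zero. With true effects d1 and d3, the expected coefficient is (0 + d1 + d3)/3, and the mean follow-up effect is (d1 + d3)/2. The ratio is 2/3 whatever the pattern:

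| Effects at baseline, month 1, month 3 | Group coefficient | Mean follow-up effect | Ratio |
|---|---|---|---|
| 0, 1, 1 | 0.667 | 1.00 | 0.667 |
| 0, 1, 0.5 | 0.500 | 0.75 | 0.667 |
| 0, 0.5, 1 | 0.500 | 0.75 | 0.667 |
| 0, 1, 0 | 0.333 | 0.50 | 0.667 |

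In the last row the effect exists only at month 1, when the virtual reality block ends, and the coefficient is one-third of it. In any one trial, a third of the observed D0 is carried into the estimate.

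A simulation (12 per arm, correlation 0.5, true effect 1.0 SD at both follow-ups, 300 runs) gave a mean group coefficient of 0.70 (Monte Carlo SE 0.02) without the interaction, in line with 0.667. The mean post-baseline contrast with the interaction was 1.00 (SE 0.02).

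**2. Power.**

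Assumptions:
- n = 12.5 per group (50 in total, about half in Spain, 1:1)
- effect of 1 SD at both follow-ups
- equal correlation ρ between visits
- two-sided 5% level, noncentral t with 2n − 2 degrees of freedom (2n − 3 with a baseline covariate)

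Standard errors in SD units:
- Group main effect over three visits: √[2(1 + 2ρ)/(3n)]. At ρ = 0.6: √[2 × 2.2/37.5] = 0.343, for an expected 0.667.
- Mean change from baseline, available once the interaction is added: √[(2/n)((1 + ρ)/2 + 1 − 2ρ)]. At ρ = 0.6: √[0.16 × 0.60] = 0.310, for an expected 1.
- Follow-up mean adjusted for own baseline: √[(2/n)((1 + ρ)/2 − ρ²)]. At ρ = 0.6: √[0.16 × 0.44] = 0.265, for an expected 1.

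| ρ | Group main effect, as written | Mean change, interaction added | Follow-up mean, own baseline |
|---|---|---|---|
| 0.4 | 54% | 71% | 90% |
| 0.6 | 46% | 87% | 95% |
| 0.8 | 40% | 99% | 99.7% |

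The model as written loses power as the correlation rises, while the other two gain.

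**3. Single visits and dropout.** At ρ = 0.6, the contrast at one follow-up visit has SE √[0.16 × (2 − 2ρ)] = 0.358 as a change (76% power) and √[0.16 × (1 − ρ²)] = 0.320 with own-baseline adjustment (85%). With about 12% dropout, n = 12.5 × 0.88 = 11, and the three columns of the table at ρ = 0.6 become 41%, 82% and 92%. The ordering does not change.

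**The case against.** The strongest objection is that silence is not exclusion. The biomarker sentence sits in a section on missing data and may only adapt the main model to one site and three visits, with the interaction taken as read. The full formula may stand in a statistical analysis plan that is not shown. This holds to the extent that nobody can say the interaction will be left out. It does not dispose of the point. The article writes this model out term by term, with its own time levels and random effects, and it names the interaction in the only other model that it describes.

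A second objection is that baseline as a response visit is no error in itself. That is right. With group-by-time in the model it is a standard analysis, and it keeps participants who have a baseline but no follow-up value. The fault lies in combining a baseline response with no interaction.

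Third, a reader might take the fall from 95% to 46% as the cost of the missing term. It is not, because that comparison also switches to own-baseline adjustment. The cost of the missing term alone is the gap between about 87% and 46%.

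Finally, a reader might infer that the non-pain secondary outcomes are wrongly analysed because the main model adjusts for baseline pain. The documents do not support this. The sentence introduces the primary analysis, where baseline pain is the outcome's own baseline. Own-baseline adjustment is planned in the covariate analyses, and the choice of covariates is deferred to the analysis plan. Even if the model is used for every outcome, adjusting for pain costs precision and does not bias a randomised comparison in expectation.

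**Conclusion.** The point holds for the biomarker model as stated. Fitted with only the listed terms, its group coefficient is exactly two-thirds of the mean follow-up effect with complete data (one-third of the month-1 effect if there is none at month 3), plus a third of any baseline imbalance. That needs no assumption about variance or correlation.

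The power loss does rest on assumptions: about 46% against 87% with the interaction, or 95% with own-baseline adjustment, for 12.5 per group, a 1 SD effect and correlation 0.6. Over correlations of 0.4 to 0.8 the figures are 54–40%, 71–99% and 90–99.7%.

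The reach is limited. The biomarkers are secondary, measured in Spain only and described as preliminary, and the primary pain analysis is not touched. The correction is still worth making, since the biomarkers are part of the stated aim. The use of baseline pain for other secondary outcomes is a lesser matter of precision, and arises only if the main model is applied to them.

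**What to change.** In the biomarker paragraph of the section on statistical population and missing data, do one of the following:

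- Add group-by-time to the stated model and report the group contrasts in change from baseline at 1 and 3 months.
- Use the 1- and 3-month values as responses, with group, time, group-by-time and the biomarker's own baseline as covariate, and report the group difference at each visit.

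The second is more precise under the assumptions above. Its small downside is that participants with no follow-up value do not contribute.

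If the main model in Statistics is also meant for the non-pain secondary outcomes, say so, and replace baseline pain with each outcome's own baseline in that model instead of leaving this to the exploratory step.

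The cost is a few words before analysis. All the values needed are already scheduled for collection.
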